# Background and Introduction

Although the scale up of antiretroviral therapy (ART) in Zambia has reached over 600,000 adults and children, ^1^ the present health care systems is neither optimally efficient nor effective. To improve both the effectiveness and efficiency of HIV care delivery from both the patient and health system perspectives, we plan to evaluate the local preferences for, and implementation of, “differentiated” delivery strategies that reduce unnecessary contact with facility-based care and improve community support for stable patients in rural and urban areas and low and high patient volume sites.

We hypothesize that differentiated care approaches will be more effective and more efficient as measured by improved patient retention in care, reduced clinic congestion, and provider and patient satisfaction. ^2-13^ Although implementers have piloted some of these strategies elsewhere, there are a dearth of examples in which they have been taken to scale, and data on their outcomes are lacking from less resourced countries outside of South Africa. Our implementation science study uses a variety of methodologies to both understand preferences and acceptability of new models of care by patients and their family members, healthcare workers (HCW), policy makers and other key stakeholders, and to rigorously, yet pragmatically produce unbiased assessments of the magnitude of benefits to the health system and to patients, along with a rich local understanding of implementation processes.

## 1.1 Rationale for study

**Continued scale up of ART using traditional facility-based ART delivery methods is likely to compound human resource and infrastructure deficiencies.** Although over 600,000 in Zambia have started treatment, acceleration of case identification as well as broadening treatment criteria mean that expected numbers may double in the next five years. “First-generation” ART services tended to be facility-based, staffed by higher-level HCW and characterized by inflexible patient appointment schedules, short visit intervals, and administrative requirements (e.g. standardized care and treatment counselling for all patients, etc). This service delivery model has persisted despite the fact that an estimated 50% of patients are stable on ART with no complaints. ^1^ This “one-size-fits-all” approach contributed to national ART retention rates of 67.4% at 24 months in 2011.

**Differentiated care – including fuller engagement of the community – may be a more effective and efficient service delivery model.** Innovative delivery strategies have begun to move away from facility to community based services. Community Adherence Groups, which emerged first in Mozambique, are patient groups of six stable individuals who take turns attending the clinic, thereby reducing the number of visits from 6-12 for each patient, to 2 each over the course of a year. This markedly reduces patient transportation burden, leverages social ties to heighten adherence to the clinic visit, and simultaneously reduces clinic volume and congestion, thus allowing providers to focus on the less stable patients who remain in the facility based model of care. While seemingly effective, issues such as selection bias, counterfactual construction, loss to follow-up, and use of viral load have not been addressed in a compelling fashion. This study will address these issues and establish the data that the Government of the Republic of Zambia will need to scale these new models nationally.

## 1.2 Significance

The existing health delivery systems for HIV infected patients are not optimal: loss to follow up exceeds 25% at one year and 33% at two years, thus threatening the gains of widespread ART roll out. ^14^ Opportunity costs for clinic attendance are high - on average, patients must travel long distances to access care and may lose an entire day of work productivity. In addition, burnt out health care workers and clinic congestion can make a clinic environment unpalatable for patients. Finally, psychological barriers, including stigma and depression, are common and can undermine motivation to continue care. These factors are all exacerbated by a one-size-fits all health delivery system and excessive demands on the patient.

Health systems are overburdened and complicated delivery algorithms tie up essential resources. A recent US Government technical review of the HIV program in Zambia recognized the serious infrastructural challenges within the current health system and the promise of care decentralized into the community as a tool to decongest overcrowded sites: *“It is clear that the public health system has already surpassed the capacity of its human resources and physical infrastructure to address the rapidly growing number of ART clients.  Although substantial improvements can be made working through the existing system, community-based models should be explored and supported by PEPFAR.”* Our goal is support the national system in Zambia to unlock existing capacity and target it toward those in need.

##

## 1.3 Aims

Our study seeks to create generalizable knowledge about the implementation process as well as the effectiveness and efficiency of a differentiated care system, by measuring patient health outcomes and implementation outcomes such as acceptability, feasibility, fidelity, and costs.

## 1.4 Specific Objectives

1.4.1 Objective 1:

**To determine the acceptability, appropriateness, and feasibility of a differentiated care system in Zambia**, by assessing perspectives of three key groups (1) patients and family members (2) health care workers and (3) government and local leaders.

1.4.1 Objective 2:

**To evaluate the effectiveness, efficiency, and health care quality of a differentiated care system that includes targeted models of care.**

Effectiveness of differentiated models of care will be assessed through retention in care, efficiency through cost-effectiveness analysis, and quality through qualitative and quantitative methods.

1.4.3 Objective 3:

**To develop a “methodologic” toolkit for assessment of local needs and preferences and for implementation during scale-up of differentiated care models in this and in other contexts**, using data from Objectives 1 and 2.

## 1.5 Audience and Stakeholder Participation

This study is a joint endeavor of the Zambian Ministry of Health (MoH), Ministry of Community Development, Mother & Child Health (MCDMCH), Bill & Melinda Gates Foundation (BMGF), and the Centre for Infectious Disease Research in Zambia (CIDRZ). Stakeholders include people living with HIV particularly the civil society organizations actively working with this population, community leaders and ordinary members in study sites, the Government of the Republic of Zambia (particularly health related line ministries and corresponding provincial, district and facility structures), the Centers for Disease Control and Prevention (CDC) in Zambia and other partners involved in HIV prevention, care and treatment in Zambia, other donors, and the men and women of Zambia. We will work closely with all stakeholders to ensure that data from this study is appreciated and understood. Where necessary, we will work with relevant technical working groups within the Ministries to adapt or develop policies to ensure that these findings are concretely translated into policy.

## 1.6 Ethical Issues

Overall, this study seeks to evaluate patient, provider, and policy maker perspectives as well as systems interventions that target health care facilities. In all instances the intervention is delivered at the clinic level but we will obtain written informed consent among both intervention and control participants. CIDRZ will work with control sites and the MOH to develop a feasible plan for offering the intervention at control sites after the study period. Such plans will take into account any changes to MOH policies, the CIDRZ funding environment, and other external factors.

For all four models, eligible patients within the intervention clinic will be offered enrollment in a systematic fashion until the site reaches the enrollment cap (see Appendix 4). Since it is expected that enrollment in the study will decrease the number of times a participant has to attend clinic (thus decreasing costs to the participant), transportation refunds will not be offered for participation. Patients who decline to consent and patients who do not meet eligibility criteria will receive standard of care at the intervention site. After the enrollment cap has been reached, the remaining patients at the intervention clinics will continue to receive the standard of care. At the time that informed consent is obtained, patients will be notified that the intervention is scheduled to last only through Month 25 of the study. CIDRZ will work with sites to create exit plans for the post-study period. Such plans will take into account any changes to MOH policies, the CIDRZ funding environment, and other external factors.

Additionally, in Objective 1, we use quantitative surveys and qualitative interviews of multiple stakeholders to understand needs and preferences. We will seek written informed consent to carry out these assessments.

This protocol, the informed consent documents, and any subsequent modifications will be reviewed and approved by the UNZA Biomedical Research Ethics Committee (BREC) and the necessary IRB’s responsible for oversight of the study. Further information on participant risks, benefits and other considerations for human participants are addressed in Section 3.5 of the protocol ‘Considerations for Human Participants’.

In each of these settings, the interviewer will provide verbal information about the study including the objectives of the study, the potential benefits and risks, and confidentiality. An information sheet, mirroring the information, which was provided verbally, will then be given to and retained by the participant. Both parties will sign a consent form. In the case of a participant being illiterate, an independent witness will additionally sign the consent form to confirm that the information provided verbally matches the written information. Privacy of individuals and confidentiality of data is detailed in Section 3.5.

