Information will be collected during the intervention period on a subset of participants in each model using a semi-structured questionnaire to assess direct and indirect health costs of the intervention. Administrative data, where needed, will also be used.

1. *Exit viral load testing and patient exit-survey*

In all four models, patients will have an exit viral load test performed at the end of the 12-month intervention period. In CAG, UAG, and Fast-Track models, participants will be administered a patient exit-survey to assess patient satisfaction and patient centeredness.

A summary of the routine schedule of activities within four models of differentiated care is shown in Appendix 5.

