### 3.2.4 Measurements

We will use information from routine clinical documentation, which includes:

1. Socio-demographic, laboratory, clinical, and pharmacy data

We will extract standard de-identified socio-demographic, laboratory and clinical data for all patients (intervention and control) from the patient’s electronic medical records.

1. Participant attendance, individual ART pick-up, and symptom assessment for UAG, CAG, and Fast-Track

We will use model specific registers that include information such as 1) Attendance, 2) Receipt of medications 3) Symptom checklist 4) Whether patient prefers to remain in care model or return to standard clinical care. This information will be entered into the study database using a tablet.

In addition, the study will also measure additional processes and outcomes related to each of the four models of care, which includes:

1. Movement between tiers for UAG, CAG and Fast-Track

The presence of symptoms or a patient’s desire to return to standard care will trigger an up-referral to the facility. Patients with acute illness, once stabilized, will be down-referred back to the model. Movement between tiers will be measured using a register that will document any up-referral after initial study enrollment. This information will be entered into the study database using a tablet. Down-referrals will be captured by measuring assigned frequency of clinic visit in the electronic medical record.

1. Patient satisfaction and patient-centeredness for UAG, CAG and Fast-Track

Patient satisfaction and centeredness will be measured as part of a semi-structured patient-exit survey that will be conducted after the 12-month intervention period.

1. Viral load testing

Viral load testing (at baseline and exit) using dried blood spot specimens will be conducted as noted in the procedures section.

1. Costing

A semi-structured costing questionnaire will be administered to a subset of intervention participants to assess direct and indirect health costs of the intervention (as noted in the procedures section). In addition, to calculate the resource use of each activity, we will use time-in-motion studies among patients and health care workers prior to and during the intervention.

1. Process data will be collected through qualitative assessments (i.e. HCW interviews during and at the end of follow-up period) and facility-level assessments (i.e. frequency of pharmacy stock outs).

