### 3.2.5 Analytic Approach and Sample Size Considerations

*a. Outcomes and Analysis*

The primary outcome in three models that target retention in care (CAG, UAG, Fast-track) is defined as time to first missed pharmacy pick-up (> 7 days late). For the START model which targets ART initiation, we use the date of ART initiation as the primary outcome. To evaluate the impact of CAG and UAG interventions, we will use Kaplan-Meier estimates of time to the primary outcome, stratified by intervention condition, using log rank tests. For Fast-track and START, our primary analysis will take a difference-in-difference approach in which we estimate the difference in the change in the rate of the outcome between intervention and control settings. In secondary analyses of the primary outcome, we will explore longer intervals of lateness that comprise a missed pharmacy visit (14 and 30 days) as well as adjustment for baseline patient characteristics. We will also explore analysis using medication possession ratio (MPR) as the outcome and other metrics of retention ^17^ that incorporate both frequency of missed visit as well as interval of time before return.

The secondary outcomes will focus on implementation and quality (see Appendix 2).

a. *Implementation Outcomes*

- *Feasibility* will be evaluated qualitatively through analysis of interviews and focus groups.
- *Costs* will be evaluated quantitatively using “bottom-up” activity-based micro-costing techniques (see Measurements section above) and “top-down” evaluation of budgets and spending reports, based on calculations of DALY’s.
- *Fidelity* of the intervention models will be assessed through estimates of the proportion of identified and eligible patients successfully enrolled in a model, the proportion of missed visits, and the proportion of CAG/UAG still functioning at the end of the 12-month intervention period.

*b. Quality Outcomes*

We use the framework offered by the Institute of Medicine to define quality outcomes.:

- *Access* will be evaluated using time (days) from positive symptom screen to appropriate referral.
- *Efficiency* will be assessed using cost-effectiveness analysis. We will consider the incremental cost per additional patient retained and the cost per death averted using effectiveness data from each model.
- *Safety* will be evaluated by estimates of the proportion of patients with appropriate laboratory monitoring and symptom screening.

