### 3.2.6 Study Timeline

For all interventions with the exception of the START model, enrollment will occur for a four-six months period (Months 10-15 on Study Timeline). Enrollment will begin on Day 1 of the enrollment period and will stop either after the target number of patients are enrolled or at the end of the four-six months enrollment period (whichever comes sooner). Implementation will occur for a twelve-month period (Months 16-27 on Study Timeline). Outcome (retention) data will be measured at Month 27 of the study.

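### Section 1.6 has patients told at consent that the intervention ends at Month 25, but section 3.2.6 runs the twelve-month implementation to Month 27

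*Protocol*

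**What the plan says.** Protocol section 1.6 fixes what patients hear about duration. When consent is taken, "patients will be notified that the intervention is scheduled to last only through Month 25 of the study". The paragraph opens by covering all four models, and its next sentences turn to exit plans that the sites will prepare for the period after the study.

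Protocol section 3.2.6 sets the calendar: "For all interventions with the exception of the START model, enrollment will occur for a four-six months period (Months 10-15 on Study Timeline"). Enrolment "will stop either after the target number of patients are enrolled or at the end of the four-six months enrollment period", whichever is earlier. Then: "Implementation will occur for a twelve-month period (Months 16-27 on Study Timeline). Outcome (retention) data will be measured at Month 27 of the study".

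Three other places give the length of the intervention without calendar months:

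- Section 3.2.3: "patients will have an exit viral load test performed at the end of the 12-month intervention period".
- Section 3.2.4 refers to a "patient-exit survey that will be conducted after the 12-month intervention period".
- Section 3.2.5 counts, as part of fidelity, "the proportion of CAG/UAG still functioning at the end of the 12-month intervention period".

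On written information, section 1.6 adds: "An information sheet, mirroring the information, which was provided verbally, will then be given to and retained by the participant".

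**The concern.** Sections 1.6 and 3.2.6 both state when the intervention is scheduled to stop, both count in study months, and they give different months. Neither is a log of changes or superseded text, and nothing in the available protocol reconciles them.

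What is at stake is the accuracy of what participants are told. Month 25 is the end date that the protocol undertakes to give them. If the trial follows section 3.2.6, the intervention continues for two months beyond that date, and the exit viral load, due at the close of the twelve months, falls after the announced end. The same month could also carry over into the information sheet and the site exit plans.

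**Working it through.** No sample size or power formula is involved. The check is a count of months, with both end months included.

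**Inputs**

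- Announced end of intervention: Month 25 (section 1.6).
- Enrolment, all models except START: Months 10-15 (section 3.2.6).
- Implementation: twelve months, Months 16-27 (section 3.2.6).
- Retention measured: Month 27 (section 3.2.6).
- Intervention length elsewhere: 12 months (sections 3.2.3, 3.2.4 and 3.2.5).
- Planned intervention participants: CAG 600, UAG 600, Fast-Track 400 (Appendix 4).

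**Step 1. Is section 3.2.6 consistent with itself?**

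Enrolment: 15 − 10 + 1 = 6 months, the upper end of its four-to-six-month range. Implementation: 27 − 16 + 1 = 12 months, as stated. It starts in the month after enrolment closes and ends in the month of outcome measurement. The section is consistent.

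**Step 2. Does Month 25 fit that calendar?**

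From Month 16 to Month 25: 25 − 16 + 1 = 10 months. This is 12 − 10 = 2 months short of the length given in section 3.2.6 and in the three other sections. As a share of the period, 2/12 = 17%.

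**Step 3. What calendar would produce Month 25?**

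A twelve-month period ending at Month 25 starts at 25 − 12 + 1 = Month 14. With enrolment opening in Month 10, it would have to close in Month 13, and 13 − 10 + 1 = 4 months, the lower end of the range. So Month 25 matches a four-month enrolment followed by Months 14-25. The available protocol gives no such window, and Months 14 and 15 fall within the stated enrolment period. Month 25 may be left over from a four-month enrolment plan, but that is an inference.

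**Step 4. How many participants could be told the wrong date?**

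600 + 600 + 400 = 1,600 intervention participants outside START. This is an upper bound: it assumes full enrolment and a consent form that repeats Month 25.

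**The case against.** The strongest reply is that the direction of the error is not proved. References to a 12-month intervention do not choose between the dates, since Months 14-25 are also twelve months. Enrolment may last as little as four months and may stop early once the target is met, so an end at Month 25 fits one permitted enrolment length. Section 5.0, listed in the table of contents as the time frame, is not available to settle it. This has some force: the sponsor may have meant Month 25. But section 3.2.6 is the dedicated timeline, agrees with itself, and fixes both the implementation window and the outcome month without making them depend on how fast enrolment goes. Section 1.6 is equally unconditional. Month 27 is the likelier figure, and whichever was meant, one of the two sections has to change.

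Other points limit the consequences, and they stand:

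- The exit survey is placed after the intervention by design, so its falling after the announced end is not a defect in itself. The exit viral load, tied to the end of the period, is the better example.
- The information-sheet sentence follows the text on Objective 1 and speaks of an interviewer, whereas section 3.2.3 gives Objective 2 consent to a research assistant. Its use for Objective 2 is likely but not certain.
- Nothing in the available text withdraws the intervention at Month 25. If section 3.2.6 is followed, participants receive it for longer than they were told, not for less time.
- START is excepted from the enrolment window in section 3.2.6, so Month 27 cannot be read across to it with confidence.

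**Conclusion.** The concern holds for CAG, UAG and Fast-Track. On the calendar in section 3.2.6, the end date that section 1.6 has patients told is two months too early, 17% of the intervention period. Up to 1,600 participants could be affected, on the condition given in step 4. The conclusion rests on section 3.2.6 being the intended calendar and covers only the text available. The consent form and sections 3.4.1, 3.4.7 and 5.0 could not be read, so they may repeat Month 25 or correct it.

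This is a minor correction to participant information. It leaves the sample size, the power, the outcome definitions and the planned analysis unchanged.

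**What to change.** In section 1.6, replace Month 25 with Month 27 for CAG, UAG and Fast-Track, and give START's end date separately because section 3.2.6 excepts it from the enrolment window. Check the consent form, the information sheet and the site exit plans for Month 25 and correct them where it appears. If the sponsor in fact intends Month 25, section 3.2.6 must change instead: enrolment to Months 10-13, implementation to Months 14-25, and the outcome to Month 25.

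The cost is one month number in the protocol, plus a wording correction in the participant documents if they carry the same figure. It needs no extra patients, data or analysis.

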# Literature Review

**The outcomes of patients in community adherence groups (CAGs) have been quantified, but the effects of a CAG as compared to patients continuing routine care has not been directly evaluated.** Data on community adherence groups (CAGs) is observational and drawn primarily from a single-arm study conducted in Mozambique. ^7,8^ Médecins Sans Frontières (MSF) pioneered the creation of CAGs ^15^ and found retention of 97.5% at a median follow-up time of 12.9 months and four-year retention rates of 92%. These studies, however, did not account for the fact that patients who are stable are selected for in these groups and there is no comparator group of comparable “stable” patients who did not join any of the groups. Rasschaert et al employed a mixed-methods approach to evaluate implementation of the CAG model in Tete, Mozambique. ^7,16^ Their evaluation provides a logic framework for the CAG intervention but does not quantify effects directly against a counterfactual.

**There is only one observational study that has evaluated urban adherence groups (UAGs) that was conducted in a township in Cape Town, South Africa.** ^6^ The clubs, consisting of individuals stable on ART for 12 months, met for 2 hours every 2 months and were facilitated by peer educators/lay counsellors who distributed pre-packaged ART and providing basic clinical consultation. This was a cohort study and included contemporaneous control patients receiving routine nurse-led care. The primary outcome was death or loss to follow-up. The secondary outcome was virologic rebound in patients supressed at study entry. At the end of the evaluation period (approximately four years), 97% of patients remained in care compared to 85% of control patients. After adjustment, participation was associated with a 57% reduction in loss to follow-up and 67% reduction in virologic rebound. There was a limited attempt at accounting for selection bias using inverse probability weighting.

**Streamlined pharmacy pick-up has been evaluated in Uganda where a cost-effectiveness analysis was conducted to compare a pharmacy-only refill program to the standard of care.**^11^ There was a non-significant decrease in odds of having a CD4 > 500 at the end of the study period with the intervention. Costs were calculated from a limited societal perspective and the incremental cost-effectiveness ratio (ICER) comparing intervention to standard of care was US $13,500 per patient with a CD4 > 500. There are no additional effectiveness studies evaluating this model of care, and none with the more comprehensive design of our proposed FAST-TRACK model.

**Although there are several studies using POC CD4 technology, few have evaluated it in the context of the HIV clinical care cascade or evaluated its effect on reducing time to ART initiation as part of a streamlined algorithm of care (such as START).**

Present day CD4 technology burdens systems and patients: at lower level facilities patients or specimens must be transported long distances. Repeatability of POC CD4 testing is excellent even with non-laboratory operators and field studies demonstrate feasibility and technical validity in program settings in Africa. No published studies have evaluated the use of a streamlined ART initiation program using POC CD4 testing.

A summary of select literature on the outcomes of differentiated care models is available in Appendix 1.

